## Abstract

**Background:**

Using kidneys from deceased donors is an available strategy to meet the growing need of grafts. However, higher incidences of delayed graft function (DGF) and acute rejection exert adverse effects on graft outcomes. Since ischemia-reperfusion injury (IRI) and ongoing process of immune response to grafts are the major causes of DGF and acute rejection, the optimal induction intervention should possess capacities of both repairing renal structure injury and suppressing immune response simultaneously. Mesenchymal stem cells (MSCs) with potent anti-inflammatory, regenerative and immune-modulatory properties are considered as a candidate to prevent both DGF and acute rejection in renal transplantation. Previous studies just focused on the safety of autologous MSCs on living-related donor renal transplants, and lack of concomitant controls and the sufficient sample size and source of MSCs. Here, we propose a prospective multicenter controlled study to assess the clinical value of allogeneic MSCs in preventing both DGF and acute rejection simultaneously as induction therapy in deceased-donor renal transplantation.

**Methods/design:**

Renal allograft recipients (n = 100) will be recruited and divided into trial and control groups, and 50 patients in the trial group will be administered with a dose of 2 × 10^6^ per kilogram human umbilical-cord-derived MSCs (UC-MSCs) via peripheral vein injection preoperatively, and a dose of 5 × 10^6^ cells via renal arterial injection during surgery, with standard induction therapy. Incidences of postoperative DGF and biopsy-proved acute rejection (BPAR) will be recorded and analyzed. Additionally, other clinical parameters such as baseline demographics, graft and recipient survival and other severe postoperative complications, including complicated urinary tract infection, severe pneumonia, and severe bleeding, will be also assessed.

**Discussion:**

This study will clarify the clinical value of UC-MSCs in preventing DGF and acute rejection simultaneously in deceased-donor renal transplantation, and provide evidence as to whether allogeneic MSCs can be used as clinically feasible and safe induction therapy.

**Trial registration:**

ClinicalTrials.gov, NCT02490020. Registered on 29 June 2015.

**Electronic supplementary material:**

The online version of this article (doi:10.1186/s13063-017-2291-y) contains supplementary material, which is available to authorized users.

## Background

Renal transplantation is the definitive solution for patients with end-stage renal failure [1]. Growing need for renal transplantation far exceeds the supply of donor organs and the shortage is becoming more severe for the increasing numbers of patients listed for transplantation. According to the Eurotransplant report, only 1788 transplant kidneys were available for 10,689 patients on the waiting list in 2014 [2]. To overcome this problem, the use of deceased donors is becoming the major source of transplants. However, in the process of deceased-donor renal transplantation, prolonged ischemic time from donor harvest to kidney reperfusion in recipients inevitably results in higher incidences of delayed graft function (DGF) and acute rejection, and causes adverse effects on graft outcome [3–6]. DGF is identified as a strong risk factor for subsequent chronic allograft dysfunction and shortened allograft survival, but current prevention methods such as the application of erythropoietin (EPO) and hepatocyte growth factor (HGF) do not demonstrate significant clinical benefit in decreasing DGF [7–11]. Moreover, prolonged ischemic time leads to a significantly earlier and greater onset of acute rejection, which also exerts an adverse effect on graft survival. Therefore, interventions aimed at both decreasing DGF and suppressing acute rejection may be a promising way to improve early graft function.

DGF is primarily a consequence of pre-transplant injury and immune responses after reperfusion. Severe ischemia-reperfusion injury (IRI) and acute kidney injury (AKI) adversely affect renal structure such as early tubular atrophy and interstitial fibrosis during transplantation using deceased donors, which is caused by accumulation of metabolic waste products such as nitric oxide (NO), superoxide anion and hydrogen peroxide to initiate oxygen-radical-induced injury and apoptosis of cell membrane [12]. As for acute rejection, mediators of the innate and adaptive immunity such as toll-like receptors (TLRs) are activated to trigger T cell clonal expansion and differentiation of effector cells, which modulate the complement cascade to aggravate donor kidney injury [13]. Hence, the optimal therapy to prevent both DGF and acute rejection for renal transplantation using deceased donors should possess capacities of both repairing renal structure injury and suppressing immune response simultaneously. However, no current induction therapies achieve this goal.

Mesenchymal stem cells (MSCs), represent significant anti-inflammatory, tissue repair and immune-modulatory properties, and suggest a novel cell-based approach in the renal transplantation. Effects of MSCs have been explored in many preclinical models of AKI [14]. MSCs can secrete numerous growth factors such as insulin-like growth factor 1 (IGF-1) and vascular endothelial growth factor (VEGF), disrupt inflammatory response in the injured kidney accounting for improving recovery from IRI [15, 16]. In the experimental models, MSCs have also been shown to inhibit T cell proliferation, modulate B cell functions and suppress natural killer cytotoxic effects, which may be applied to inhibit allograft rejection and induce transplant tolerance [17]. Therefore, MSCs have potential benefits to prevent both DGF and acute rejection. However, few clinical data on MSCs applied to transplantation have been published, in which potential disadvantages of results had negative effects on clinical application of MSCs, due to lack of concomitant controls and sufficient sample size and source of MSCs [18–20].

In our previous study, we performed human umbilical-cord-derived MSCs (UC-MSCs) to kidneys from donors after cardiac death (DCD) and found a significant effect on reduction of both antibody-mediated rejection and AKI [21]. Now, we will carry out a prospective multicenter controlled study to clarify the clinical value of UC-MSCs as induction therapy to prevent both DGF and acute rejection in deceased-donor grafts. Here, we propose the protocols of this study.

## Methods/design

### Objectives

The objective of this study is to assess the clinical value of human UC-MSCs as induction therapy to prevent both DGF and acute rejection via different ways of administration in deceased-donor renal transplantation.

### Endpoints

#### Primary endpoints

The primary endpoints of this study include DGF during one week post transplantation, and biopsy proven acute rejection (BPAR) over one year.

#### Secondary endpoints

The secondary endpoints are severe opportunistic infections related to opportunistic infection and pulmonary and urinary tract infection over one year postoperatively.

### Study design

This is a prospective multicenter controlled study including three kidney transplant institutions (the third affiliated hospital of Sun Yat-sen University, Zhujiang hospital of Southern Medical University, and the second affiliated hospital of Guangzhou Traditional Chinese Medicine University). The protocol has been approved by the Ethics Committee of Human Study at the three institutions, which were established according to the Operational Guidelines for Ethics Committees that Review Biomedical Research developed by the World Health Organization (WHO) [22].

No organs from executed prisoners will be used in the study, and procurement of kidneys from all donors will be conducted in accordance with the WHO principles, Declaration of Helsinki and Istanbul declaration [23, 24]. Organ donation and recovery will be conducted by organ procurement organizations in the three kidney transplant institutions, which were established by the National Health and Family Planning Commission of China. Before procurement, written consent will be obtained from the donor’s immediate family, agreeing to donation of the kidney and withdrawal of life support. The obtained consent for donation will be then reported to the Organ Donation Committee, which supervises the donation process.

All the participants in this study will provide informed, written consent to undergo this study. Participants receiving renal transplantation with deceased-donor grafts will be recruited and randomly divided into two groups. The trial group will undergo peripheral vein injection of human UC-MSCs in the 48 hours before the operation, and renal arterial injection during the operation. The control group will not receive UC-MSC treatment. All the participants will have standard induction therapy. All the participants will be recruited from the three transplant units and meet the eligible criteria. The Standard Protocol Items: Recommendations for Interventional Trials (SPIRIT) Figure is provided in Fig. 1.

**Fig. 1 Fig1:**
[figure not shown]
Summary of enrollment, interventions, assessments, and timing for measurements (Standard Protocol Items: Recommendations for Interventional Trials (SPIRIT)). DGF, delayed graft function; BPAR, biopsy-proven acute rejection

### Eligibility criteria

#### Inclusion criteria

Female or male aged between 18 and 60 yearsSubjects who conform to the indications for renal transplantationSubjects who are willing to participate in the study and have provided written informed consent prior to any study procedureSubjects receiving a first kidney graft from deceased donors

#### Exclusion criteria

Subjects who are lost to follow-up.Contraindications to undergoing renal transplantation, such as patients with evidence of active infection, suffering from hepatic failure, an active autoimmune disease, documented HIV infection, active hepatitis B, hepatitis C or tuberculosis (TB), cytomegalovirus (CMV), BK virus, aspergillosis, histoplasmosis or mycobacteria other than TB, or a previous bone marrow transplant.Occurrence of severe adverse events, such as toxic effects, CMV reactivation, and post-transplant lymphoproliferative disease.Double organ-transplant recipients.Treatment with any investigational drug used after transplantation.Malignancy within the past 5 years according to current transplantation inclusion criteria.Known recent drug abuse.Recipients of ABO blood-type incompatible transplants.

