### Randomization and blinding

The participants will be assigned to either the UC-MSCs treatment group or the control group in a 1:1 ratio using a block randomization method. A randomization list has been pre-generated. The participants will be blinded to the treatment group throughout the study (Fig. 2).

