DGF is defined as urine output < 1000 ml/day in first 48 hours or failure of serum creatinine to decrease by 10% in the first 48 hours postoperatively, according to Shoskes [26]. BPAR is classified according to the Banff 2013 classification [27]. Renal color ultrasound will be performed at 1 day, 7 days, 1 month, 3 months, 6 months, and 1 year postoperatively. Time-zero biopsy and protocol biopsies at 14 days and 12 months postoperatively will be performed. When acute rejection is suspected clinically, renal allograft biopsy will also be carried out. The incidence of BPAR at 2 weeks, 1 month, 3 months, 6 months, and 1 year after the operation will be recorded. For opportunistic infection, the incidence of CMV, EBV, and BK-viremia will be measured in blood samples, and pulmonary and urinary tract infection will be monitored at 3 months, 6 months, and 1 year after the operation.

Additionally, laboratory examinations such as routine blood and urine tests, tests of liver and renal function, and concentration of CNI will be assessed once a week in the 3 months after the operation, once every 2 weeks in months 3 to 6, and once a month in months 6 to 12.

Adverse side effects in the UC-MSC treatment group may include fever, uncommon arrhythmia and allergic reaction. Adverse events will be recorded and treated. The trial blood samples will be collected to examine safety.

We will make every effort to minimize missing data. Trial enrollment and follow-up procedures will be reviewed during bi-monthly conference calls. We will report rates of missing data for each outcome by study arm and send missing data reports to the sites.

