### Statistical analysis

Parametric (e.g., analysis of variance (ANOVA)) and non-parametric (e.g., Kruskal-Wallis test) statistical tests will be applied using the SPSS version 21 (SPSS Inc., Chicago, IL, USA) for the data analysis. Multi-level regression analysis will be used to examine differences between trial arms for the endpoints. The logistic model will be applied for binary endpoints, and linear regression will be for continuous endpoints. All analyses will follow intention-to-treat principles and a pre-specified analysis plan. As for missing data values, we will apply mean imputation and regression imputation where rates are low, and consider multiple imputations where they exceed 10%. Since multiple tests are performed simultaneously, the Bonferroni correction will be made during analysis to determine the critical *P* value for significance. *P* values < 0.05 will be considered as statistically significant. The SPIRIT checklist is provided in Additional file 2.

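### Two exclusion criteria describe events that arise after randomisation and contradict the intention-to-treat analysis and the safety and infection outcomes

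*Protocol article*

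**What the plan says.** The Exclusion criteria of the protocol article include three items that refer to the course of the trial and not to the patient's state at entry:

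- "Subjects who are lost to follow-up"
- "Occurrence of severe adverse events, such as toxic effects, CMV reactivation, and post-transplant lymphoproliferative disease"
- "Treatment with any investigational drug used after transplantation"

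Other sections say the following:

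- **Statistical analysis:** "All analyses will follow intention-to-treat principles and a pre-specified analysis plan". Missing values are to be imputed, with multiple imputation considered when more than 10% are missing.
- **Secondary endpoints:** severe opportunistic infection and pulmonary and urinary tract infection over one year.
- **Data collection and postoperative monitoring:** "the incidence of CMV, EBV, and BK-viremia will be measured in blood samples". Adverse events are to be recorded, and missing-data rates reported by outcome and arm.
- **Primary endpoints:** delayed graft function (DGF) in the first week and BPAR over one year.

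**The concern.** An exclusion criterion decides who enters a trial. Loss to follow-up, a severe adverse event or a CMV reactivation during follow-up can be known only once a patient is in it. Used as exclusions, such events turn eligibility into a filter on outcome: randomised patients would leave the comparison because of how they fared. Intention-to-treat is meant to prevent this.

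Two things are at stake. Severe events that the trial sets out to record could disappear from its safety and infection results, although the safety of allogeneic cells is one of its stated aims. And one-year BPAR could be compared in a subset formed after randomisation, so that the arms are no longer comparable by design.

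**Working it through.** **Step 1: can the two items be read as baseline criteria?**

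- Loss to follow-up presupposes enrolment.
- CMV present at entry is already covered by a separate item on contraindications to transplantation: "cytomegalovirus (CMV), BK virus, aspergillosis, histoplasmosis or mycobacteria other than TB, or a previous bone marrow transplant". The CMV reactivation named in the severe-adverse-event item must therefore mean something else.
- Inclusion requires a first kidney graft, and a previous bone marrow transplant and double organ transplantation are exclusions. Post-transplant lymphoproliferative disease (PTLD) then most naturally means disease after the study transplant.
- Assignment is "in a 1:1 ratio using a block randomization method". The article does not state the moment of randomisation, but "The trial group will undergo peripheral vein injection of human UC-MSCs in the 48 hours before the operation", so allocation must come before surgery. Events during post-transplant follow-up come after it under any feasible timing.

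**Step 2: can they be read as rules for ending study treatment?** Under UC-MSC treatment there is one infusion before surgery and one injection during it. After surgery no study treatment is left to end. A reaction to the first infusion could bear on the second; loss to follow-up, CMV reactivation or PTLD later in the year could not. No sentence limits the items to treatment.

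**Step 3: does the dropout allowance reconcile them?** The Sample size section goes from 44 to 50 per arm for 10% dropout: 44/0.9 = 48.9, rounded up to 49 and set at 50. Ten per cent of 50 is 5 patients per arm. That is an allowance for lost information. Under intention-to-treat those 5 stay in the analysis set, with missing values handled as planned; an exclusion criterion takes them out. The rest of the sample size calculation does not bear on this point.

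**Step 4: what would exclusion do to BPAR?** The documents give no exclusion rates, so these inputs are assumptions except the first:

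- p = 0.167, the control-group acute rejection figure in the Sample size section. It is a 6-month figure, used here as the true one-year risk in both arms, so there is no real effect.
- s = share of an arm excluded: 20% (10 of 50) for UC-MSC and 10% (5 of 50) for control.
- r = share of excluded patients who have BPAR.

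Retained BPAR = (p − s·r)/(1 − s).

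| r | UC-MSC, s = 0.20 | Control, s = 0.10 | Difference |
|---|---|---|---|
| 0.40 | (0.167 − 0.080)/0.80 = 10.9% | (0.167 − 0.040)/0.90 = 14.1% | −3.2 points |
| 0.167 | (0.167 − 0.0334)/0.80 = 16.7% | (0.167 − 0.0167)/0.90 = 16.7% | 0 |
| 0.10 | (0.167 − 0.020)/0.80 = 18.4% | (0.167 − 0.010)/0.90 = 17.4% | +0.9 points |
| 0.05 | (0.167 − 0.010)/0.80 = 19.6% | (0.167 − 0.005)/0.90 = 18.0% | +1.6 points |

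More unequal exclusion widens the gap: s = 0.30 against 0.10 with r = 0.30 gives (0.167 − 0.090)/0.70 = 11.0% against (0.167 − 0.030)/0.90 = 15.2%. Exchanging s between the arms reverses every sign. Equal s with equal r gives no difference between arms.

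**Step 5: the other outcomes.** Severe adverse events, and CMV reactivations counted as severe, would be missing from the comparison. The CMV result would be 0 against 0 only if every CMV event were treated as an excluded event. DGF is judged on the first 48 hours, before most of the listed events could occur. It is less exposed, unless patients excluded later are removed from the DGF analysis as well.

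**The case against.** The strongest reply is that the explicit analysis statements point the other way. Intention-to-treat, imputation, recording of adverse events, CMV measurement at 3, 6 and 12 months and missing-data reports by arm are all promised, and nothing says that data are removed. On this view the exclusion list is loose drafting. This stands in part, and it sets the limit of the point: the text supports a contradiction and does not establish what the investigators will do.

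Four stronger readings are tempting, and the documents do not support them:

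- **Safety data are deleted.** This would follow from applying the criteria literally; it is not stated.
- **The CMV endpoint is emptied.** CMV reactivation is named as an example of a severe adverse event. Blood monitoring covers CMV incidence more widely, and EBV, BK virus, pulmonary and urinary infections are also assessed.
- **The exclusions fall on the UC-MSC arm and favour it.** The item does not limit toxic effects to those of the cells. Both arms receive antithymocyte globulin, methylprednisolone, mycophenolate and a calcineurin inhibitor, so the listed events can occur in either. No rate or direction is given, and the table shows bias both ways.
- **The investigational-drug item is the same fault.** It can be read as barring patients who are in, or planned for, another drug study, which can be judged at enrolment. It is ambiguous.

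What the reply does not do is make the two remaining items compatible with intention-to-treat. Nor is this a detail left to a fuller document: one positive statement conflicts with others.

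**Conclusion.** The point holds as a contradiction that must be resolved. Loss to follow-up and the occurrence of severe adverse events stand as exclusion criteria although they arise after randomisation, and no sentence confines them to baseline or to treatment. They cannot be applied together with the intention-to-treat statement, the imputation plan, and infection and adverse events as outcomes.

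Its size depends on how the criteria are applied. If they are ignored in practice, the harm is unclear wording. If they are applied, severe events leave the safety and infection comparison, and one-year BPAR is biased by an amount and in a direction that the documents do not determine. In the 20% against 10% illustration with no true effect, the spurious difference runs from 3.2 points in favour of UC-MSC (r = 40%) to 1.6 points against it (r = 5%). These figures rest on assumed exclusion shares and assumed risks among excluded patients, and they show only that the bias need not be negligible. That randomisation precedes the events is inferred from the pre-operative infusion.

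**What to change.** Amend the protocol as follows:

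1. Remove loss to follow-up and the occurrence of severe adverse events from the exclusion criteria.
2. State that every randomised patient stays in the assigned arm and in the analysis set for both primary endpoints and all safety endpoints.
3. Count severe adverse events, CMV reactivation and PTLD as outcomes.
4. Handle loss to follow-up as missing data or by censoring.
5. Reword the investigational-drug item so that it can be judged at enrolment, and keep patients who receive such a drug later in the analysis.

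If any item was meant as a rule on giving study treatment, state it separately, with continued follow-up and analysis of those patients. Its clinical content is for the investigators.

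The cost is a short wording amendment and continued follow-up of patients already enrolled. The article reports that recruitment was still open at submission. Any patient already taken out under these items should be restored to the analysis set as far as the data allow.

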### Treatment methods

#### UC-MSC treatment

A target of 2 × 10^6^ UC-MSCs per kilogram body weight will be injected via the peripheral vein during the 48 hours before renal transplantation. The dose of UC-MSCs administered via the renal artery during the implantation surgical procedure is 5 × 10^6^ cells.

#### Standard induction therapy

The standard induction therapy is described as follows: all recipients receive antithymocyte globulin (ATG) 50 mg for 3 days and methylprednisolone (MP) with a total amount of 2.0 g. Then, prednisone (Pred) is taken orally at the initial amount of 30 mg, and tapered at a dose of 2.5 mg per week, to the maintaining dose of 5 mg per day. Mycophenolate (MMF) is taken from that day after the operation at a dose of 1.0 g twice a day. Calcineurin inhibitors (CNI), (such as cyclosporine (CsA) or FK506) are given 3 days after the operation.

### Isolation of UC-MSCs

The human UC-MSCs used in this study will be isolated after birth with the written consent of the parents. The human UC-MSCs will be harvested in a total volume of 100–120 ml. The processing and expansion of the cells will take place at the Good Manufacturing Practice (GMP) Stem Cell Laboratory Facility of Sun Yat-sen University, as previously described [25]. The characterization of the final product will be determined by the flow cytometric analysis, which expresses CD90, CD73, CD105, CD44, and CD166. Before infusion, the human UC-MSCs will be subjected to aerobic, anaerobic and fungal cultures and tested for mycoplasma infection, and then confirmed to be sterile.

